## Abstract

**Background:**

HIV prevalence remains high among men who have sex with men (MSM) in the United States, yet the majority of research has focused on MSM as individuals, not as dyads, and has discussed HIV risks primarily in the context of casual sex. Nexus is an online prevention program that combines home-based HIV testing and couples HIV testing and counseling (CHTC). It allows partners in dyadic MSM relationships to receive HIV testing and care in the comfort of their designated residence, via video-based chat. By using video-based technologies (eg, VSee video chat), male couples receive counseling and support from a remote online counselor, while testing for HIV at home.

**Objective:**

This randomized control trial (RCT) aims to examine the effects of video-based counseling combined with home-based HIV testing on couples’ management of HIV risk, formation and adherence to explicit sexual agreements, and sexual risk-taking.

**Methods:**

The research implements a prospective RCT of 400 online-recruited male couples: 200 self-reported concordant-negative couples and 200 self-reported discordant couples. Couples in the control arm will receive one or two home-based HIV self-testing kits and will be asked to report their results via the study’s website. Couples in the experimental arm will receive one or two home-based HIV self-testing kits and will conduct these tests together under the facilitation of a remotely located counselor during a prescheduled VSee-based video CHTC session. Study assessments are taken at baseline, as well as at 3- and 6-month follow-up sessions.

**Results:**

Project Nexus was launched in April 2016 and is ongoing. To date, 219 eligible couples have been enrolled and randomized.

**Conclusions:**

Combining home-based HIV testing with video-based counseling creates an opportunity to expand CHTC to male couples who (1) live outside metro areas, (2) live in rural areas without access to testing services or LGBTQ resources, or (3) feel that current clinic-based testing is not for them (eg, due to fears of discrimination associated with HIV and/or sexuality).

**Trial Registration:**

ClinicalTrials.gov NCT02335138; https://clinicaltrials.gov/ct2/show/NCT02335138 (Archived by WebCite at http://www.webcitation.org/6qHxtNIdW)

## Introduction

HIV prevalence remains high among men who have sex with men (MSM) in the United States [1]. Recent research has drawn attention to the role of male dyads in the US HIV epidemic, with primary partners identified as the source of approximately one-third [2] to two-thirds [3] of new HIV infections. Given these estimates, a significant paradigm shift in HIV prevention is needed. Efforts have traditionally focused on MSM, in particular gay-identifying men, (1) as individuals versus dyads and (2) as having been the focus of messages about HIV risks, primarily in the context of casual sex. Recent research findings have illustrated high rates of sexual risk behavior for HIV with primary and casual partners, low rates of disclosure of potentially risky episodes with casual partners to primary partners, and reduced frequency of HIV testing among male couples [4-10]. In addition, relationships may convey a misplaced sense of protection [11,12], to some degree created by the historical prevention focus on reducing numbers of sexual partners among MSM [13]. The Office of the US Global AIDS Coordinator, through dissemination of prevention guidelines for MSM in the President’s Emergency Plan for AIDS Relief-supported countries, now recommends couples HIV testing and counseling (CHTC) for male couples [14].

CHTC has been used as an HIV prevention intervention for heterosexual couples in Africa for over 20 years [15]. Labeled as a “high leverage HIV prevention intervention” by the US Centers for Disease Control and Prevention (CDC) [16], CHTC is considered an effective approach to HIV prevention among male couples. The difference between CHTC and individual HIV testing and counseling is that both partners of the male couple receive counseling and testing together at the same time [17]. During the CHTC session, the counselor learns about the couple’s relationship and provides tailored counseling and HIV prevention recommendations based on the characteristics of the couple’s relationship and their joint HIV status [17]. Through the adaptation of CHTC and the high acceptability among MSM [15,18], preliminary data from MSM in three US cities—Atlanta, Chicago, and Seattle—demonstrate the readiness of US MSM to receive and use CHTC [19,20]. Preliminary data also suggests that male couples receiving CHTC do not report increased levels of intimate partner violence (IPV) or relationship dissolution [21]. CHTC is now considered by the CDC to be an effective public health strategy and is currently being implemented in over 40 US states [17,22].

A critical aspect of CHTC involves discussing a couple’s sexual agreement. Sexual agreements refer to mutually understood rules between two partners that describe the kinds of sexual behavior that are allowed within and outside of their relationship [23]. Sexual agreements are common among male couples [5,23-30]. In CHTC, male couples discuss their sexual agreements, role-play with the counselor about how they would communicate about breaking their sexual agreement to their partner, and develop an HIV prevention plan based on their sexual agreement and couple HIV serostatus. Research regarding male couples’ sexual agreements has shown that men are less likely to practice concurrent condomless anal intercourse (CAI) if they value and commit to their agreement and if they perceive their main partner to be dependable and investing in the relationship [29,31-33]. Additionally, promoting positive relationship dynamics has the potential to reduce couples’ risk for HIV, as increased trust, communication, commitment, and social support are shown to be associated with lower odds of breaking a sexual agreement, which can ultimately reduce unique HIV risks (eg, CAI) for the couple [4].

In addition to CHTC, another HIV testing option is home-based HIV testing, which was approved by the US Food and Drug Administration in 2012 [34]. Some have argued that the lack of direct counseling with home-based testing may prevent MSM from (1) fully understanding the results, (2) adopting safer preventive strategies, and/or (3) successfully linking to care if newly HIV positive [35]. One way to address the lack of counseling for home-based HIV testing may be through the use of remote online counseling delivered through video-chat software. Online counseling offers a convenient, confidential, and user-controlled opportunity to provide support and information to individuals who otherwise may not be willing or able to access services in person. Telemedicine modalities, such as email, instant messaging, chat rooms, video conferences, and interactive media, have provided online counseling services for people suffering from disabilities, depression, and anxiety; for survivors of trauma; and for cancer treatment [36]. Although the use of telemedicine to address HIV is a fairly recent development, evidence from diverse settings suggests it is feasible, acceptable, and effective [36-38]. A number of HIV prevention interventions have been designed to deliver messages and counseling through use of the Internet [39-42]; the results indicate that increases in knowledge, self-efficacy, and motivation for behavior change can be achieved with the participant sitting remotely at their computer. Few online services, however, have been developed to facilitate HIV testing and none have been tailored for couples. Furthermore, the majority of interventions have been delivered through text-based communication, which fails to capture important verbal and visual cues (eg, tone of voice and body language) of clients.

A vital cornerstone to prevention and linkage to care is HIV testing [43]. This paper describes the protocol for a new randomized controlled trial (RCT) that combines the CDC-recommended prevention strategy of CHTC with home-based testing for male couples via video-based counseling and testing. By using video-based technologies (eg, VSee video chat), male couples receive counseling and support from a remote online counselor, while testing for HIV at home. This combination of HIV testing efforts is needed and timely because few interventions exist for male couples, especially those who live in rural areas and areas with few LGBTQ resources. This RCT aims to examine and compare the intervention’s effects on the relationship’s ability to manage HIV risk, formation and adherence to explicit sexual agreements, and sexual risk-taking between self-reported concordant-negative and self-reported discordant male couples. Participants complete surveys at baseline, 3 months, and 6 months. It is hypothesized that couples exposed to the intervention will learn communication skills and receive psychoeducation that allows them to work together on HIV prevention planning. As a result, it is hypothesized that couples exposed to the intervention will be more likely to report discussing and forming sexual agreements and be more likely to adhere to agreements, yet also more likely to disclose if they break their agreements.

The theoretical basis for intervention is the Couple’s Interdependence Theory (CIT) [44], a framework that combines both interdependence theory and communal coping perspectives and captures constructs central to the intervention. The framework guides the selection of measures of behavior change within the couple’s relationships. Through interdependence, both members of the couple will rely on themselves and on each other to reach individual- and/or couple-positive and/or couple-negative healthy behaviors. These outcomes will either improve or detract from the quality of the couple’s relationship. With this in mind, communal coping assists couples in achieving positive healthy behaviors that benefit both members of the couple as they cooperatively communicate to reach their desired goals [44]. These measures relate to the intervention in two ways. First, some aspects of communication and decision making within the partnership may influence the efficacy of the intervention; couples with more constructive communication styles may benefit from CHTC than would couples with less constructive communication styles. Second, some aspects of partnerships, such as efficacy around implementing behavioral change, may benefit more from CHTC. In this way, changes in key characteristics of the partnerships may be in the causal pathway between the intervention and the adoption of greater health-enhancing behaviors (ie, reduction in CAI outside of the relationship) within the partnership. The causal pathways are conceptualized as follows: couples exposed to the intervention package will receive opportunities to talk together about HIV, sexual health, and sexual agreements within their relationship through the assistance of a trained CHTC counselor and will have the ability to self-test for HIV as a couple at home. This may in turn impact communal coping, use of coping, and transformation of motivation. This may lead to initiation and maintenance of health-enhancing behaviors, which is conceptualized as reduction in sexual risk-taking (eg, CAI) within and outside of the relationship relative to couples who self-test for HIV at home without the presence of a counselor. In the research design, predisposing factors, outcome efficacy—the shared desire for the same outcome (ie, HIV prevention strategies)—and couple efficacy are collected separately from each member of the male couple before the HIV testing intervention is delivered, and will again be collected at 3-month and 6-month follow-up assessments.

## Methods

### Description of Trial and Intervention

#### Design

The research activities involved a blind prospective RCT of approximately 400 online-recruited male couples—200 self-reported concordant-negative couples and 200 self-reported discordant couples. Couples in the control arm will receive one or two home-based HIV self-testing kits and will be asked to report their results via the study’s website. One kit will be provided for each person who reports to have previously tested HIV-negative or unknown status; partners in serodiscordant couples who report living with HIV will not be retested. Couples in the experimental arm will receive one or two home-based HIV self-testing kits and will conduct these tests together under the facilitation of a remotely located counselor during a prescheduled VSee-based video CHTC session.

#### Participants

Participants for each male couple must meet the following eligibility criteria: (1) two men who have been in a sexual relationship with each other for more than 6 months; (2) >18 years of age; (3) both participants not having been tested for HIV in the last 3 months, or for serodiscordant couples, the negative partner not having tested for HIV in the last 6 months; (4) reporting no IPV or coercion within the last 12 months; (5) willing to have HIV test kits delivered to an address they provide; (6) have access to the Internet within their home, or the home of at least one partner; and (7) be either self-reported concordant HIV negative or self-reported HIV serodiscordant. Participants for the trial are being recruited from across the United States, with recruitment via online advertisements placed on key social media websites (eg, Facebook and Instagram) and social media sites aimed specifically at MSM (eg, Grindr and Scruff). When men click on the advertisement, they are taken to a page containing basic study information, including a short description of study activities. If they express an interest in participation, they are then taken to the study consent form and if they consent, they are directed to a short eligibility screener. Men who (1) do not consent, (2) do not meet the eligibility criteria, or (3) do not provide an email for a main partner—defined as a sexual relationship with “a man who you feel committed to above all others”—are taken to a screen thanking them for their interest. Men who are eligible to participate must provide an email address for their main partner so that they can be enrolled in the study together. Further, eligible men able to participate and that provide their partner’s email address are directed to a registration process. During the registration process, both partners provide their contact information, including an email address, a mobile phone number, and a mailing address; they are also asked to provide a nickname or preferred name of choice. Once both partners have (1) completed the consent forms, (2) completed the screening questionnaire, (3) proven eligible for the study, and (4) registered on the study website, a joint email is sent to both partners asking them to complete the baseline questionnaire, individually.

#### Randomization

Upon individual completion of the baseline survey by both partners, couples are randomized to either the home-based HIV testing arm or video-based CHTC with home-based HIV testing arm using a stratified 1:1 treatment allocation. The strata are based on two levels of serostatus: seroconcordant negative and serodiscordant. The treatment assignments are generated with the use of a pseudo-random number generator with permutated blocks that are used to ensure balance within stratum between the numbers of couples assigned to each treatment. The randomization process generates one of two emails to both study participants for the enrolled male couple, indicating whether they will be receiving home-based HIV testing or video-based CHTC with home-based HIV testing.

#### Intervention

The proposed intervention is a combination of home-based HIV testing and CHTC offered remotely via VSee video chat. In the control arm, couples receive one or two home-based HIV testing kits based on the couple’s serostatus; the partner living with HIV in a serodiscordant couple does not repeat HIV testing. These kits sent to couples in the control arm contain one or two HIV testing kits as well as instructions on how to use the kits and how to report their test results in the study portal. In the experimental arm, couples receive one or two home-based HIV testing kits and complete the testing while undergoing a remote, VSee video-based CHTC session. Individual participants testing positive in either the experimental or the control condition are linked to their preference of local HIV care-specific resources within 48 hours. They will receive another HIV test at their preferred local HIV care-specific resource to validate the preliminary positive test result. These participants will receive follow-up from the CHTC counselor at 1-week, 1-month, and 3-month postresult of HIV-positive status to assess their engagement in care.

For couples randomized to the experimental arm, an email informs them that they have the opportunity to receive one or two home-based HIV testing kits and to take part in a video-based counseling session. The email provides details on the expected content of a CHTC session, the expectation that both partners will need to conduct their individual HIV tests and receive their results together in the presence of a remote counselor, as well as further logistical information (ie, length of the counseling session). From this email, couples are instructed to log on to the study website to order their HIV testing kits, with the same options as the control arm. Figure 1 shows the log-in page that users see when logging on to the Project Nexus website. For those randomized to receive HIV home testing with CHTC, they are asked to select a CHTC appointment time via an electronic calendar, which is shown in Figure 2. To allow intent-to-treat analysis, couples who do not complete the CHTC session and do not schedule an appointment, as well as couples in the control arm who do not report their HIV test results, are able to move on to take the 3-month and 6-month surveys.

The CHTC session is conducted via video chat using VSee. Figure 3 is an example of the VSee interface that participants see when waiting for their prescheduled counseling session to begin. The session is conducted by a counselor who is trained in CHTC and will last approximately 30-45 minutes. Pretest counseling focuses on the couple’s relationship, their perceived HIV risk factors, and focuses on their sexual agreement. Both partners individually conduct their own HIV test and read their individual results together, as instructed by the counselor. Participants are asked to show the counselor their test result; the counselor then confirms the test result for accuracy of interpretation. Figure 4 is the interface the participant sees when entering their HIV testing result to the Nexus website. Posttest counseling focuses on dyadic prevention messages and revisits the couple’s HIV risk concerns and sexual agreements in light of their test results. The counselor records the couple’s HIV test results in the couple’s study file. The counselor is trained to keep focus on the couple in the event that an HIV-positive result is given during a CHTC session. While a focus on the immediate needs of the HIV-positive partner is required, the discussion remains focused on how the couple can work together to keep the positive partner healthy and to keep the risk of HIV within, and not outside of, the relationship with other partners, while also meeting the needs of both partners within the male couple. If both couples are seroconcordant negative, the counselor discusses strategies that will minimize the risk of HIV transmission within and/or outside the relationship. The prevention-counseling element of the CHTC session focuses on talking the couple through prevention options and asking them to consider which prevention options may work best based on their relationship needs, context, and unique risk profile.

**Figure 1 figure1:**
[figure not shown]
Project Nexus website log-in page.

**Figure 2 figure2:**
[figure not shown]
Calendar function for selecting a couples HIV testing and counseling (CHTC) appointment.

**Figure 3 figure3:**
[figure not shown]
VSee session interface.

**Figure 4 figure4:**
[figure not shown]
HIV test results reporting page on Nexus website.

### Preliminary Data

An online survey of 1285 MSM from across the United States was conducted to examine willingness to use the proposed intervention (unpublished data). Respondents were recruited through targeted advertisements on Facebook over 10 days from October to November 2012. Of the 907 men who self-reported a negative HIV serostatus and provided complete data, 72.0% (653/907) reported they would be likely to use a home-based HIV test, 69.0% (626/907) reported they would be likely to use CHTC, and 75.0% (680/907) reported that they would be likely to use a home-based HIV test together with a VSee video-based CHTC session. The willingness to use the proposed intervention did not vary by age (*P*=.60), race (*P*=.91), recent (ie, <12 months) HIV testing behavior (*P*=.43), or recent CAI (*P*=.39). Among those with main partners (510/907, 56.2%), 82.0% (418/510) reported they would likely use the intervention. Among those who reported recent physical violence from an intimate partner (55/502, 11.0%), 67% (37/55) reported they would likely use the intervention. Emory University Center for AIDS Research also funded a trial of Skype-based counseling with 15 male couples from Atlanta to examine feasibility and acceptability of the video-chat counseling session. Although the trial did not incorporate HIV testing, 15 male couples were recruited using the same online recruitment methods as proposed in this intervention. Couples completed a baseline survey describing recent sexual risks and sexual agreements in their relationships; then each couple underwent an approximately 45-minute counseling session via Skype video-based chat. During the session, the Emory-based counselor talked to the couple about their sexual agreements and their management of HIV risks, and then referred them to local services. Approximately half of the couples were in monogamous relationships; the mean relationship duration was 17 months. A total of 10 couples had formalized agreements around sex outside of the relationship, which ranged from monogamy to allowing sex with outside partners under certain conditions. Couples then completed an online survey about their experiences with the Skype video-based counseling session. Satisfaction was universally high—mean satisfaction was 4.8 out of 5 and 100% of participants said they would recommend the service to other male couples. Crucially, 100% of couples stated that they would be willing to include HIV testing in the video-based counseling session, with the main reasons being “convenience” and “having access to counseling while testing at home.”

### Outcomes: Overview

The study outcomes are based on the conceptual model of CIT [44]. All measures are collected via the baseline, 3-month, and 6-month online surveys. Primary outcomes are the initiation and maintenance of health-enhancing behaviors. Secondary outcomes measure relationship characteristics.

### Primary Outcomes

Initiation and maintenance of health-enhancing behaviors are conceptualized as including two sets of outcomes: sexual agreements and sexual risk-taking as well as linkage and retention to HIV care.

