#### Sexual Risk-Taking

The definition of at-risk sex will be serostatus specific. For serodiscordant couples, at-risk sex will be CAI with either their main or outside partners. For seroconcordant-negative and seroconcordant-positive couples, at-risk sex will be CAI with outside sex partners. While data on PrEP use and adherence will be collected, the definition of at-risk sex focuses on condom use given the CDC recommendation for continued condom use for those adopting PrEP. The incidence of at-risk sex acts will be calculated as an incidence density, with the numerator being the number of individual at-risk sex acts and the denominator being person-years of follow-up time. Comparisons of the incidence of at-risk sex acts will be made by comparing incidence densities between the two arms. Incidence rates per couple-year of follow-up will be estimated and compared using exact methods based on the Poisson distribution by using the GEE approach. Baseline covariates include race, age, and duration of relationship. Period incidence rates—6-monthly incidence density rates—of at-risk sex will be estimated by performing a GEE Poisson regression analysis of the 6-monthly counts. This will be implemented using the PROC GENMOD procedure by SAS (SAS Institute Inc) [56] and using an exchangeable correlation structure for the repeated observations of couples. The incidence density ratio, or incidence rate ratio (IRR), is the ratio of the incidence density in one treatment group (intervention arm) to that of another group (control arm). Results by each baseline covariate will be summarized as the IRR and the 95% confidence interval. These analyses will be descriptive and include analyses stratified by race/ethnicity. Prevalence of each outcome will be calculated and prevalence of outcomes will be compared in the control and intervention groups using chi-square tests or Fisher’s exact tests, as appropriate.

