#### Sexual Agreements

Separately tabulated data about disclosure of sex outside the relationship and percentage of couples with agreements involving sex outside the primary relationship will be developed. These analyses will be descriptive and include analyses stratified by race/ethnicity, study arm, and couple serostatus. These analyses will also characterize the prevalence of agreements about sex outside relationships, the extent to which those agreements are adhered, and any shift of adopting safer sexual behaviors with outside partners, again stratified by race/ethnicity and study arm. A focus of the analysis will be identifying differences across the study arms in the percentages of couples who report a shift to safer sexual agreements at follow-up. In addition, the Actor-Partner Interdependence Model (APIM), which uses the dyad (eg, couple) as the unit of analysis, will be used to predict how an individual and his partner’s reports of dyadic characteristics—described within Lewis’ model [44]—affect whether the individual formed, changed, and kept the sexual agreement he had with his main partner [31]. Procedures for using SAS to calculate actor-partner effects with dichotomous outcomes with male couples (eg, indistinguishable dyads) have previously been reported in detail [31] and will be used for the proposed RCT.

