### Sample Size

The goal is to enroll and maintain a sample of 400 male couples: 200 serodiscordant and 200 seroconcordant couples, 100 of each couple per arm (experimental vs control). To achieve this, the intervention aims to screen approximately 1000 male couples—500 serodiscordant and 500 seroconcordant male couples—and will exclude those with a recent (<12 months) history of IPV. Assuming 15% of male couples have a recent history of IPV, this will produce approximately 850 couples for randomization, 425 per arm. Allowing for 20% loss to follow-up and additional 20% relationship dissolution, this will produce a sample of 400 male couples who are expected to complete the prospective RCT. The sample size is calculated based on the detection of significant changes in each of the main outcomes (ie, changes in sexual risk-taking, such as CAI), formation and adherence to explicit sexual agreements, and relationship functioning for the management of HIV risk. As an example, we will assume that about 25% of male couples change agreement status after couples counseling and we will use a two-sample test of binomial proportions with type I error rate at 5%. Using these assumptions, it is determined that 52%, 67%, and 85% statistical power is necessary to detect a difference of 10%, 12%, and 15%, respectively, in a change-of-agreement status between the two arms within seroconcordant or serodiscordant groups (ie, comparing 150 male couples per arm). In other words, under the same conditions, the probability is .52, .67, and .85 that the lower bound of the confidence interval for the proportion change in agreement status in the intervention arm is at least 3%, 5%, and 8% different than the proportion in the control arm, respectively, when the alternative hypothesis is true. If data is pooled across seroconcordant and serodiscordant couples, assuming that combining data makes sense in terms of the magnitude and direction of the intervention effect, then 81%, 92%, and 99% statistical power is necessary to observe differences of 10%, 12%, and 15%, respectively (ie, comparing 300 male couples per arm). In this case, at least 80% statistical power will be necessary to detect as little as a 5% difference between the lower bound of the confidence interval for the proportion in the intervention versus the control arm. Based on discussions with participant advocates and partnered community-based organizations, it is projected that any difference exceeding 5% would be scientifically meaningful and would have public health impact. The analysis also considers differences in linkage to HIV care among HIV-positive individuals in each arm, but it is not powered to detect significant differences, given the small number of incident positive cases.

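### The article gives two conflicting lists of primary or main outcomes, powers a different agreement outcome from the one its analysis focuses on, and names no deciding outcome or time point

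*Protocol article*

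**What the plan says.** All references are to the protocol article.

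- Primary Outcomes describes the primary tier as "two sets of outcomes: sexual agreements and sexual risk-taking as well as linkage and retention to HIV care". Outcomes: Overview adds: "Secondary outcomes measure relationship characteristics".
- Sample Size says: "The sample size is calculated based on the detection of significant changes in each of the main outcomes". The list that follows is sexual risk-taking, then "formation and adherence to explicit sexual agreements, and relationship functioning for the management of HIV risk". Linkage to care is not in it. The end of the same section says linkage is not powered because few incident positive cases are expected.
- The worked example in Sample Size concerns couples who change agreement status, in either direction, analysed by a "two-sample test of binomial proportions" with 5% type I error. No other significance level is given in the article.
- Under Statistical Analysis, Sexual Agreements says: "A focus of the analysis will be identifying differences across the study arms in the percentages of couples who report a shift to safer sexual". The quoted sentence is about the couple's agreement as reported at follow-up, and it gives no month.
- Under Statistical Analysis, Sexual Risk-Taking compares incidence densities between arms by a rate ratio and then adds: "Prevalence of each outcome will be calculated and prevalence of outcomes will be compared in the control and intervention groups using chi-square tests". Fisher's exact test is named there as the alternative.
- Surveys are taken at 3 and 6 months. Neither is named as deciding.

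**The concern.** Which outcomes carry the trial's conclusion depends on the section read. A gain in relationship functioning alone would be a secondary result under Outcomes: Overview but a result on a main outcome under Sample Size. Linkage is primary in one place and set aside as not powered in another, yet Statistical Analysis, Linkage to Care still tests it for significance between arms.

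The agreement domain has a similar split. A couple that moves to a less safe agreement counts as an event in the powered comparison but not in the comparison the analysis focuses on, so the stated power does not belong to the analysis that would be reported.

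The outcomes can also disagree: couples may form or change agreements while condomless acts do not fall. With no deciding contrast fixed, the choice of what counts as success could be made after the results are seen.

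**Working it through.** **1. The lists side by side**

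| Outcome | Outcomes: Overview and Primary Outcomes | Sample Size | Statistical Analysis |
|---|---|---|---|
| Sexual agreements | primary | main; example is any change of status | focus on shift to safer |
| Sexual risk-taking | primary | main | rate ratio, and prevalence tests |
| Linkage to care | primary | not in the list; not powered | tested for significance |
| Relationship functioning | secondary (as relationship characteristics) | main | scale comparisons and longitudinal models |

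The lists differ in both directions: one outcome is promoted and another dropped.

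**2. Reproducing the stated power**

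Inputs from Sample Size: about 25% change status, differences d of 10, 12 and 15 points, 5% type I error, 150 couples per arm within a serostatus group and 300 pooled. Sidedness is not stated; two-sided reproduces the figures. The arms are set at p1 = 0.25 - d/2 and p2 = 0.25 + d/2.

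Power = Φ{[d - 1.96·√(2·0.25·0.75/n)] / √[(p1(1-p1) + p2(1-p2))/n]}

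For n = 150 and d = 0.10: (0.100 - 1.96 × 0.0500) / 0.0497 = 0.04, so power is 51.6%.

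| Couples per arm | Stated | Recomputed |
|---|---|---|
| 150 | 52/67/85% | 51.6/67.2/85.5% |
| 300 | 81/92/99% | 80.9/92.6/99.0% |

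The stated figures are therefore those of a single test of change in agreement status at two-sided 5%. They say nothing about the other main outcomes.

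**3. What several tests would do, as an assumption**

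Assume that any one significant result counts as success, that each test is two-sided 5%, and that no outcome has a true effect. None of this is stated in the article. For k independent tests the error is 1 - 0.95^k; for correlated tests it was simulated with equal correlation (400,000 draws).

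| Tests | Correlation 0 | 0.5 | 0.8 |
|---|---|---|---|
| 3 | 14.3% | 12.5% | 9.9% |
| 4 | 18.5% | 15.7% | 11.5% |
| 8 (4 outcomes, 2 months) | 33.7% | 25.0% | 15.7% |

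Three tests means either the three domains under Primary Outcomes or the Sample Size list with agreement formation and adherence taken as one item. Four tests separates those two.

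**4. Power at the targeted couple numbers**

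The same section targets 100 couples per arm in each serostatus group, which is 200 per arm pooled. The same formula gives:

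- Pooled, n = 200, d = 0.10: (0.100 - 1.96 × 0.0433) / 0.0430 = 0.35, so 64%. For 12 and 15 points: 79% and 94%.
- Within a group, n = 100: 37/50/69%.

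**The case against.** The strongest reply is that much of this belongs to a statistical analysis plan or full protocol that is not shown. Testing order, an alpha split and operational definitions are commonly left there. The article attaches 5% to one test introduced as an example and writes no rule by which any single significant result wins. Parts of the agreement and risk-taking analyses are called descriptive. At-risk sex is analysed as a rate over a 6-monthly period and the scales are modelled longitudinally, so separate month 3 and month 6 tests are not specified. Declaring linkage unpowered is open disclosure, and sizing a trial partly on a secondary outcome is not in itself an error.

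All of that stands against the error rates in step 3, which are conditional and cannot be presented as properties of the plan. The missing alpha split alone would not be a finding. It does not answer the conflict between the lists: an analysis plan cannot follow both, and identifying the primary outcome is the protocol's job. The descriptive label does not settle it either, because Sexual Risk-Taking still provides formal arm comparisons and Sexual Agreements makes arm differences a focus.

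**Conclusion.** The article contradicts itself on which outcomes are primary or main, and it powers one agreement outcome while focusing its analysis on another. It fixes no deciding contrast or month. These conclusions rest on the text alone.

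A reader might infer that every main outcome is tested at 5%, that any one success suffices, and hence that the trial's false-positive chance is about 13-25%. The documents do not support that. It needs an unstated success rule, an unstated level for all but one test, and an assumed correlation of 0.5 with three to eight tests. What can be said is hypothetical: under an any-one-wins rule at two-sided 5%, about 10-19% for three to four outcomes (correlation 0.8 to 0), and about 16-34% if four outcomes were each tested at both months.

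The point should be settled before outcome analysis, because it changes what the trial can conclude.

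**What to change.** 1. Use one list in Outcomes: Overview, Primary Outcomes and Sample Size, with relationship functioning and linkage to care (stated as not powered) secondary in all of them.
2. Name one deciding contrast with its exact definition and time point. An example is the couple-level percentage with a shift to a safer agreement at month 6, intervention against control, two-sided 5%. Define which moves between agreement categories count as safer, and use the same definition in Sample Size and in Statistical Analysis, Sexual Agreements.
3. Test the at-risk-sex incidence rate ratio already described in Sexual Risk-Taking next, in a fixed sequence and only if the first test is significant. If both are to be co-primary, use Holm at an overall 5%. Which outcome goes first is the sponsor's choice.
4. Label the other agreement measures, month 3 results and prevalence tests as supportive.
5. Restate power for the named contrast at 200 couples per arm pooled and 100 per arm per serostatus group, in place of 300 and 150. The assumed rate will need revisiting if the outcome becomes a shift to safer agreements, since 25% was assumed for any change.

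The cost is wording only, and recruitment was still under way when the article was written (219 couples randomized). A fixed sequence leaves the first test its full 5%. The drawbacks are that later outcomes cannot support a confirmatory claim if the first test fails, and that the restated power is lower: about 64/79/94% pooled for 10/12/15 points under the Sample Size assumptions.
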